**Figure 1 F1:**
[figure not shown]
**Flow chart of treatment schedule**. (1) Daily documentation until day 7 has to be done in the patient chart. CRF documentation will be done on day 1, 4, ±1 and 7 + 1 after surgery. Adverse events have to be documented as soon as they occur. (2) Has to be done daily with respective documentation in the patient file. (3) CRF documentation will be done on these days. (4) Generally if the patient is discharged before day 7, all documentation required until the day of discharge (e.g. day 1, 4, etc.) has to be completed together with the discharge page (visit 3). However if discharge is on day 1, 4 + 1 or 7 + 1 the documentation of the respective day (day1, 4 or 7) can be omitted (with the exception of the header which has to be filled in); only the discharge page (visit 3) needs to be filled in instead.

### Eligibility

Detailed inclusion and exclusion criteria are specified in table 2. Patients are screened consecutively for eligibility in the participating centre after approval of the study protocol by the local ethics committee of the Ludwig-Maximilians-University (LMU), Munich, Germany. A contract has been signed by Aesculap AG and the participating centre for correct conduction of the trial according to Good Clinical Practice. The participating surgeons performing the intervention have been instructed by detailed manuals.

### Consent

The participating centre recruits trial patients from its patients who are scheduled for an elective primary median abdominal incision with a expected length of ≥15 cm. All patients who seem to fit to the in- and exclusion criteria will be asked whether they are willing to participate in the trial and they will be informed about the purpose of the trial, the operation modalities, data management, and their possibilities and risks. Interested patients will be screened according to inclusion and exclusion criteria and included into the trial after written Informed Consent has been obtained from the patient.

### Randomization

Block randomisation with randomly varying block sizes and a ratio 1:1 to the two treatment arms will be used in order to provide treatment groups of approximately equal sizes. The block length will be documented separately and will not be disclosed to the investigators. Randomisation code was generated by the statistician of the Clinical Trials Centre (ZKS), Freiburg, Germany. To guarantee concealment of the randomisation, it will be performed using sealed opaque envelopes which were produced by the ZKS and are kept at the study centre. Randomisation will take place before abdominal wall closure. If there is an explicit need to unblind during the follow up, the randomisation envelopes can be used to unblind the patient.

### Intervention

After the surgical procedure, the abdominal incision is closed from the caudal and cranial end up to the middle with a monofilament suture loop by using the continuous suture technique. Up to 3 cm of the incision will be left open in the middle of the incision. A-Part^® ^Gel is prepared and brought under the incision through the open part in the middle. A-Part^® ^gel syringe is placed to one end of the incision. The A-Part^® ^Gel is applied along the partly sutured incision while pressing out slowly the viscous gel onto the abdominal wall. This procedure is repeated on the other half of the incision, and when the syringe is taken out from the open middle part of the incision. Thereafter the abdominal incision is completely closed according to the INSECT suture technique [28] and the skin closure is performed with staples. It is recommended to use 10 ml of A-Part^® ^Gel for covering 10 cm of incision. The A-Part^® ^Gel is only applied by a trained surgeon.

### Study Device

A-Part^® ^Gel is a sterile, absorbable, translucent adhesion barrier composed of two unmodified water soluble biocompatible polymers: polyvinyl alcohol (PVA) and carboxymethylcellulose (CMC) [13,26]. Both components PVA and CMC are already used for various biomedical applications [10,16,17,22-25]. PVA is used in drug coating, contact lenses, tendon repair or artificial articular cartilage [14,15]. CMC is used as an additive in tablets, suspensions and creams. PVA is biologically inert and is not degraded in mammal metabolism [29,30]. As a water soluble polymer, PVA is mainly secreted by the kidneys, only small amounts are excreted via faeces. CMC is a cellulose derivative that is already been used as barrier material for adhesion protection with good results regarding efficacy and biocompatibility [10,22-25].

A-Part^® ^Gel does not promote bacterial growth. A-Part^® ^Gel is indicated for use in patients undergoing abdominal or pelvic surgery. A-Part^® ^Gel is intended to reduce the incidence, extent and severity of post-operative adhesions between the abdominal wall and the underlying viscera such as omentum, small bowel, bladder and stomach and between the uterus and surrounding tissues such as tubes and ovaries, large bowel and bladder. A-Part^® ^Gel serves as a temporary absorbable barrier separating the parietal and visceral peritoneal tissue surfaces immediately after surgery. A-Part^® ^Gel acts as a physical barrier for adhesiogenic tissue while the normal tissue repair takes place [26]. After placement on the tissue A-Part^® ^Gel immediately attaches to the surface; A-Part^® ^Gel is elastic, soft and translucent [26]. A-Part^® ^Gel is absorbed and undergoes renal excretion within approx. 6 weeks [18].

### Statistical consideration and sample size estimation

The aim of this study is a first assessment of the safety of the application of A-Part^® ^Gel as an adhesion prophylaxis after major abdominal surgery as compared to control. Sample size considerations are not based on statistical calculations, but on the feasibility of recruitment. It is planned to randomise 60 patients between A-Part^® ^Gel and control, because this is expected to be feasible within six months from a single centre. This phase I study is conducted as a first application of A-Part^® ^Gel in man, and its aim is to receive first safety data as compared to control. The power considerations are based on the specific observation of two major complications of abdominal surgery "occurrence of wound healing impairment or postoperative peritonitis within 28 (+10) days after surgery" as a primary combined endpoint. It is assumed that without application of the A-Part^® ^Gel wound healing impairment will occur with a probability of about 5-10% and postoperative peritonitis will occur with a probability of about 2-5% [31-33]. This leads to the assumption that the combined endpoint will occur in the control group with a probability of about 10-15%. It is the aim of the study to show that the application of A-Part^® ^Gel does not lead to an unacceptable increase in the probability of occurrence of the combined endpoint i.e the non-inferiority of A-Part Gel^® ^as compared to the control. Under the assumption that the application of A-Part^® ^Gel does not increase the probability of the combined endpoint, this study can show at one-sided significance level α = 5% with a power of 80% that the absolute difference of the event probabilities between both treatment groups is not larger than 20-25% [34].

The two-sided 90%-confidence interval for the absolute difference (A-Part^® ^Gel minus control) of probability of occurrence of the primary endpoint will be calculated. If the upper bound of this confidence interval is below 0.25, the hypothesis that the difference is 0.25 or larger will be rejected. Adverse event incidences, wound healing impairment, postoperative peritonitis, adhesion and complication rates will be calculated with two-sided 90% confidence intervals.

The safety analyses will be conducted in the safety population, including all randomized patients with group assignment by treatment received. All analyses will be done with the Statistical Analysis System (SAS).

No interim analysis is planned for this trial.

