## Conclusions

This prospective, randomised, controlled, patient - and observer- blinded, single centre study evaluates as a primary endpoint, if the application of A-Part^® ^Gel is safe as adhesion prophylaxis, in comparison to a non-treated control group, during and after abdominal surgery.

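### Excluding a 25-point increase is treated as non-inferiority, but 0.25 is what 60 feasible patients can exclude, not an increase stated to be acceptable

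*Protocol article*

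**What the plan says.** All of this is in the protocol article, section Statistical consideration and sample size estimation.

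- **Size.** Sixty patients, 30 per arm (the per-arm figure is under Design). The number is justified by feasible recruitment and expressly not by a statistical calculation.
- **Control rate.** The article assumes that "wound healing impairment will occur with a probability of about 5-10% and postoperative peritonitis will occur with a probability of about 2-5" per cent, and continues: "This leads to the assumption that the combined endpoint will occur in the control group with a probability of about 10-15" per cent.
- **Aim.** To show that the gel "does not lead to an unacceptable increase in the probability of occurrence of the combined endpoint", which the same sentence glosses as non-inferiority to control.
- **Power.** If the gel changes nothing, "this study can show at one-sided significance level α = 5% with a power of 80" per cent that "the absolute difference of the event probabilities between both treatment groups is not larger than 20-25" per cent.
- **Rule.** A two-sided 90% confidence interval is calculated for gel minus control. "If the upper bound of this confidence interval is below 0.25, the hypothesis that the difference is 0.25 or larger will be rejected".

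**The concern.** A non-inferiority margin should be the largest increase one is prepared to accept. Here the order is reversed: feasibility fixes the sample size, the sample size fixes the excludable difference at 20-25 points, and 0.25 then becomes the decision limit. The aim stated just before gives that limit the meaning of no unacceptable increase. The text contains no step from what can be excluded to what is acceptable.

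The range for the control rate compounds this. It starts at 10%, although the low ends of its two components add up to less, so the limit looks smaller relative to the background rate than the article's own components imply.

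At stake is the primary safety conclusion of a first application in man. A pass would support a statement that a very large increase has been ruled out, but the article gives it a stronger name.

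**Working it through.** **Inputs** (same section unless noted): 30 per arm (Design); control rate p = 0.10 to 0.15; true difference 0 for the power statement; one-sided α = 0.05; power 0.80; limit 0.25. No dropout is stated, so 30 evaluable patients per arm are assumed.

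**1. The plan's own figure.** Excludable difference = (z₀.₉₅ + z₀.₈₀) × √(2p(1−p)/30) = (1.645 + 0.842) × √(2p(1−p)/30).

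- p = 0.10: 2.486 × 0.0775 = 0.193
- p = 0.15: 2.486 × 0.0922 = 0.229

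The stated 20-25 points therefore reproduces after rounding. With a constrained-null (Farrington-Manning) variance, power for the 0.25 limit with 30 per arm is 89% at p = 0.10 and 82% at p = 0.15.

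**2. What the limit means as a rate.** 0.10 + 0.25 = 0.35, and 0.15 + 0.25 = 0.40. As ratios, 0.35/0.10 = 3.5 and 0.40/0.15 = 2.7.

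**3. Chance of passing.** Exact binomial enumeration of all tables with 30 per arm; a pass means an upper 90% bound below 0.25.

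| True control → gel | Wald | Newcombe | Farrington-Manning |
|---|---|---|---|
| 10% → 10% | 92.8% | 92.1% | 92.1% |
| 10% → 20% | 49.5% | 49.0% | 48.9% |
| 10% → 30% | 13.1% | 13.3% | 13.0% |
| 10% → 35% (limit) | 5.3% | 5.5% | 5.3% |
| 15% → 15% | 84.8% | 84.7% | 84.6% |
| 15% → 30% | 24.8% | 26.1% | 24.8% |
| 15% → 40% (limit) | 5.1% | 5.8% | 5.1% |

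The choice of interval hardly matters.

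**4. Observed tables.** Wald upper bound = difference + 1.645 × √(p₁(1−p₁)/30 + p₂(1−p₂)/30), gel versus control.

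- 5/30 v 2/30: 0.100 + 0.135 = 0.235, passes
- 6/30 v 3/30: 0.100 + 0.1502 = 0.2502, just fails
- The most gel events that pass are 5 against 3 control events, 6 against 4, and 7 against 5

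**5. Control range.** The probability of either event is at most the sum of the two.

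- Low ends: at most 5% + 2% = 7%; under independence 1 − 0.95 × 0.98 = 6.9%
- High ends: at most 10% + 5% = 15%; under independence 1 − 0.90 × 0.95 = 14.5%

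The upper end agrees with the article. The lower end of 10% does not follow from the low ends of the components. At p = 0.07 the excludable difference is 2.486 × √(2 × 0.07 × 0.93/30) = 0.164, and the 0.25 limit corresponds to a gel rate of 32%. Over 7-15%, the excludable difference is about 16-23 points.

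**The case against.** The strongest defence is that the article hides nothing. It calls the trial a first assessment, says that the size rests on feasibility, and words the decision sentence modestly: only the hypothesis of a difference of 0.25 or more is rejected. The difference with its 90% interval is already the planned analysis. Taking 0.25 rather than 0.20 is coherent too, since at a 15% control rate a 0.20 limit has only 66-70% power with 30 per arm. All this stands. It justifies the sample size and the calculation, but not naming a pass non-inferiority or the absence of an unacceptable increase. A clinical reason for 25 points may exist in the full protocol, which is not shown; the article itself derives the figure only from power.

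On the control range, the figures are approximate and rest on references not available here. Assuming 10% rather than 7% is also conservative for power, and it does not alter the rule. This part is minor.

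A reader might infer more than the documents support:

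- **That the rule lets a 2.7- to 3.5-fold increase through.** Those ratios are the boundary under test. A gel truly there passes about 5% of the time, which is the nominal error rate.
- **That an observed doubling generally passes.** With 3 control events (10%), 6 v 3 fails. Doublings or worse, such as 5 v 2, pass only when the control arm has at most 2 events, below the assumed rate.
- **That the rule concerns serious complications.** The article calls them major, and Table 1 includes wound-edge necrosis and infection of the superficial incision.
- **That the article already claims safety.** The Abstract's discussion and the Conclusions only pose the question whether the gel is safe.

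**Conclusion.** The concern holds as a mismatch between rule and conclusion. The rule is a valid 5% test that the increase is below 25 points. The article attaches to it a judgement about acceptability that it does not support. The practical size is seen in true effects short of the limit: a doubling would pass about 49% of the time from 10%, or about 25% from 15%. A pass is therefore weak evidence against a doubling of these major complications. Separately, the lower end of the control range should be about 7%, not 10%.

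These figures assume 30 evaluable patients per arm and the article's control rates. They hold across the three interval methods tried. Nothing here says what increase would be acceptable.

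**What to change.** Change the section Statistical consideration and sample size estimation only:

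1. Replace the wording on an unacceptable increase and non-inferiority with a statement such as: the trial can rule out an absolute increase of 25 percentage points or more in the combined endpoint of major complications; this does not by itself establish non-inferiority or safety.
2. Say that the result will be interpreted through the already planned difference and its two-sided 90% confidence interval.
3. Restate the control range as about 7-15%, and the difference excludable with 80% power as about 16-23 points.

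The Abstract and Conclusions need no change. No patients are added, which matters because the article reports recruitment complete in December 2009. The cost is a weaker headline claim.

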**Methods/Design:**

This is a prospective, randomised, controlled, patient blinded and observer blinded, single centre phase I-II trial, which evaluates the safety of A-Part^® ^Gel as an adhesion prophylaxis after major abdominal wall surgery, in comparison to an untreated control group. 60 patients undergoing an elective median laparotomy without prior abdominal surgery are randomly allocated into two groups of a 1:1- ratio. Safety parameter and primary endpoint of the study is the occurrence of wound healing impairment or peritonitis within 28 (+10) days after surgery. The frequency of anastomotic leakage within 28 days after operation, occurrence of adverse and serious adverse events during hospital stay up to 3 months and the rate of adhesions along the scar within 3 months are defined as secondary endpoints. After hospital discharge the investigator will examine the enrolled patients at 28 (+10) days and 3 months (±14 days) after surgery.

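### The only non-inferiority test groups patients by treatment received, with no as-randomised comparison stated, so a gel-arm patient not given the gel counts as a control

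*Protocol article*

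**What the plan says.** In the protocol article, the section on statistical consideration and sample size gives the aim as showing that the gel "does not lead to an unacceptable increase in the probability of occurrence of the combined endpoint i.e the non-inferiority of" the gel against control. The decision rule is: "If the upper bound of this confidence interval is below 0.25, the hypothesis that the difference is 0.25 or larger will be rejected". The interval is two-sided at 90%, for gel minus control.

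The same section fixes the grouping for the safety analyses, whose population is described as "including all randomized patients with group assignment by treatment received". The Methods/Design part of the abstract shows that this covers the primary test: "Safety parameter and primary endpoint of the study is the occurrence of wound healing impairment or peritonitis within 28 (+10) days after surgery". The objectives section likewise makes safety, measured by these two complications, the primary objective.

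Three design facts bear on the rule:

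- **Timing.** The Randomization section places allocation before the abdominal wall is closed. Under Intervention, the gel is applied afterwards, through a gap in the partly closed incision.
- **Blinding.** The Design section lists the patient and the ultrasound assessor as blinded. It does not list the operating surgeon.
- **Control.** The control condition is no treatment.

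**The concern.** Because control is no treatment, a patient allocated to the gel who does not get it has received the control condition. The stated rule moves that patient, with any event, into the control group. The step happens after allocation and can depend on what an unblinded surgeon sees in the operating field. If the reason for omission is related to the risk of wound complications or peritonitis, the groups compared are no longer those formed by randomisation.

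At stake is the single pass/fail conclusion of a first-in-man safety trial. Moving an event out of the gel arm lowers the gel rate and raises the control rate at once, so in a trial of 60 one patient has visible leverage. Treatment-received grouping is usual for adverse event tables. It is less suitable as the only basis for a formal non-inferiority claim.

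**Working it through.** **Inputs from the article.** 30 patients per arm (Design); control rate 10-15%, true difference 0, one-sided 5%, power 80%, margin 0.25 (statistical section). The article names no interval method; the Wald interval is used here, with others as a check. The number of gel-arm patients not given the gel is not in the document; 1 or 2 is an assumption.

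**The plan's own figure.** The margin that 30 per arm can exclude with 80% power is (1.645 + 0.842) × sqrt(2p(1−p)/30).

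- p = 0.10: 0.193
- p = 0.15: 0.229
- with a continuity correction of 1/30 added: 0.226 and 0.263

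The stated 20-25% is consistent with this range.

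**Effect of regrouping.** Upper bound = d + 1.645 × sqrt(p1(1−p1)/n1 + p0(1−p0)/n0), where d = p1 − p0, gel minus control.

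| Case | Gel v control | d | SE | Upper bound | Result |
|---|---|---|---|---|---|
| A, as randomised | 7/30 v 4/30 | 0.100 | 0.099 | 0.263 | fail |
| A, one patient with an event moved | 6/29 v 5/31 | 0.046 | 0.100 | 0.210 | pass |
| B, as randomised | 7/30 v 5/30 | 0.067 | 0.103 | 0.236 | pass |
| B, one event-free patient moved | 7/29 v 5/31 | 0.080 | 0.103 | 0.2501 | fail |
| C, as randomised | 7/30 v 3/30 | 0.133 | 0.095 | 0.289 | fail |
| C, two patients with events moved | 5/28 v 5/32 | 0.022 | 0.097 | 0.181 | pass |

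Moving the patient with an event shifts the bound by 0.263 − 0.210 = 0.053 toward the gel. Moving the event-free patient shifts it by 0.2501 − 0.236 = 0.014 against the gel.

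**Sensitivity to method.** Case A reverses under Wald, continuity-corrected Wald, Newcombe and Farrington-Manning. So does case C with two patients moved. Which pass-to-fail results occur depends on the method; B reverses by Wald, but only just.

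**How often.** These are probabilities, by enumeration of the Wald rule, that the as-randomised result fails and moving gel-arm patients with events makes it pass:

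| True rates, gel v control | One moved | Two moved |
|---|---|---|
| 10% v 10% | 5.6% | 6.8% |
| 15% v 15% | 9.5% | 13.7% |
| 20% v 10% | 22% | 38% |
| 35% v 10% (at the margin) | 7.4% | 21% |

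These are upper limits, because they take it as given that the crossovers happened and that every moved patient had an event.

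**The case against.** The strongest reply is that treatment-received grouping is a sound choice for a question of harm. As-randomised grouping can hide harm: if 2 of 30 gel-arm patients are never exposed, a true excess of 25 points shrinks to 25 × 28/30 = 23.3 points, inside the margin. This stands, and it is why the as-treated analysis should not simply be replaced.

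Second, crossover may be rare. The gel is a single application by a trained surgeon soon after allocation. Table 2 excludes emergency surgery, intra-abdominal infection and procedures needing more than two drains. Difficulties found earlier in the operation may be known before the envelope is opened. This also stands: the number is probably small, and with no crossovers the two analyses are identical.

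Third, the article is a condensation. The full protocol or analysis plan may add an as-randomised analysis. The point is therefore confined to the rule that the article does fix for its primary test.

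A reader might go further and infer that the rule biases the result in the gel's favour only, because surgeons would withhold the gel in contaminated or difficult cases. The document does not support that. It describes no withholding, gives no crossover rate and links no omission to risk. Case B shows that moving an event-free patient works against the gel.

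**Conclusion.** The point holds as a weakness in the chosen analysis; it is not a contradiction or a numerical error. The sole non-inferiority test rests on a grouping that can depend on decisions made after allocation, and the article states no as-randomised comparison beside it. The direction of any bias depends on who is moved: patients with events shift the bound toward the gel, and event-free patients shift it less, the other way.

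One patient can reverse the verdict, but only when the result lies near the margin. The fail-to-pass reversals shown also need the moved patient to have had an event. Under the plan's assumption of equal rates, the upper limits run from 5.6% (one moved, 10%) to 13.7% (two moved, 15%). All of this assumes one or two crossovers, a figure the document does not give. The change is worth making because it is cheap and guards against error in both directions.

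**What to change.** State that the primary endpoint is tested twice, once as randomised and once by treatment received, and that the hypothesis of a difference of 0.25 or more is rejected only if the upper 90% bound is below 0.25 in both. The first analysis guards against selection after allocation; the second guards against dilution of a harm. Keep treatment-received grouping for the adverse event and serious adverse event tables.

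The cost is two sentences and one extra run of the same procedure. Power falls slightly if crossovers occur and is unchanged if they do not. The article reports recruitment as complete, but grouping is an analysis decision, so the as-randomised result can still be reported beside the other.
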